#### Cost-effectiveness analysis

A trial-based cost-utility analysis (CUA: cost-per-QALY) will be performed from a societal perspective, extrapolated to a life-time horizon. Quality of life and cost questionnaires will be filled out by the patients at discharge and at 3, 6, and 12 months after trauma. Average discounted costs and QALYs will be compared according to intention-to-treat, using net-benefit analysis, and using multiple imputations to account for missing data. Estimated societal costs will include hospital costs (estimated from study registrations), other healthcare (using iMCQ questionnaire), and productivity (using iPCQ questionnaire). Healthcare will be valued using Dutch reference prices, including time and travel costs. Productivity losses will be valued using the friction-cost method (and the human-capital method as sensitivity analysis). A state transition model will be used to extrapolate survival and other outcomes beyond the trial duration, to a life-time horizon. QALYs will be calculated using the Dutch tariff for the EQ-5D-5L measures.

#### Missing data

Missing baseline data will be multiply imputed (*n* = 5), assuming data to be missing at random.

All analyses will be performed using the R statistical software (latest available version) with the required add-on R packages.

### Data monitoring

#### Data collection and protection

Data will be collected, by dedicated research nurses and investigators, using Castor EDC, a web-based secured data capture platform. All subject data will be pseudonymized by assigning study numbers to each subject. The key to these study numbers is only available to the study team and an independent monitor from the LUMC. Data will be collected and stored for a period of 25 years. Biological samples will only be stored for the purpose of additional research if the patient has given consent. A SPIRIT diagram of the recommended content for the schedule of enrollment, intervention and data collection is included in Fig. 3.

**Fig. 3 Fig3:**
[figure not shown]
SPIRIT diagram of the recommended content for the schedule of enrollment, interventions, and assessments. *Abbreviations*: C1-INH, complement 1-inhibitor; TIL, therapy intensity level; (S)AEs, (serious) adverse events; ICP, intracranial pressure; CT, computed tomography; ICU, intensive care unit; LOS, length of stay; GOSE, Glasgow Outcome Scale Extended; QoLiBri, Quality of Life after Brain Injury Scale; iPCQ, iMTA Productivity Cost Questionnaire; iMCQ, iMTA Medical Cost Questionnaire; SF-36, Short-Form 36; EQ-5D-5L, 5 Level EuroQoL 5-Dimensional Questionnaire

#### Data and safety monitoring

An independent Data Safety Monitoring Board (DSMB) will monitor the safety of the trial with access to unblinded data regarding (S)AEs, suspected unexpected serious adverse events (SUSARs), and mortality. No interim analysis on the efficacy will be performed for this trial due to the relatively small sample size and the nature of a phase II trial focusing on safety. The DSMB will meet dependent on inclusion rate, with scheduled meetings after inclusion of 10, 30, 60, and 106 patients. The DSMB can advise the principal investigator to prematurely terminate the study if there is evidence of an unacceptable risk for trial subjects based on SAE reporting, outcome, and case fatality. Monitoring and auditing in all sites will be executed by monitors according to the pre-defined monitor plan. This will be independent from investigators and the sponsor, and they will ensure that adequate enrollment is met.

#### Safety and adverse event analysis

Safety analyses, as part of the primary endpoint, will be based on the safety set, consisting of the pre-defined SAEs, and will comprise standard descriptive methods. Changes from baseline will be summarized using standard statistical characteristics and shift tables. Details of the pre-defined SAEs, signs, and symptoms will be collected including details of onset, resolution, frequency, severity (mild, moderate or severe), seriousness, relationship to the drug, effect on the study drug, treatment administered, and outcome. Moreover, suspected unexpected serious adverse reactions (SUSARs) will be registered.

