### Objectives

The main objective of the CIAO@TBI trial is to determine the safety and efficacy of C1-INH in patients with s-TBI. The primary endpoints are (1) efficacy: intracranial pressure (ICP) directed Therapy Intensity Level (TIL), GOSE at 6 months after discharge, and (2) safety: complication rate during hospitalization.

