### Trial population and eligibility

All TBI patients presenting to participating hospitals are potentially eligible for this trial. The inclusion criteria are (1) age > 18 years, (2) clinical diagnosis of TBI with GCS < 13 on admission (with visible intracranial pathology on CT), and (3) invasive intracranial pressure monitoring by intra-parenchymatous transducer or ventricular catheter placement and management of increased ICP for at least 24 h. The exclusion criteria are (1) a clear, non-traumatic cause of low GCS on admission (e.g., toxic or cardiac cause); (2) not expected to survive more than 24 h after admission with the decision to abstain from aggressive treatment and induce palliative care; (3) brain death on arrival in the participating centers; (4) severe pre-trauma disability, defined as being dependent on other people; (5) known prior history of sensitivity to blood products or C1-INH; (6) patients with a history of hereditary angioedema (if known at admission); (7) patients with a history of thrombosis (deep vein thrombosis, cerebral venous sinus thrombosis, or pulmonary embolism) (if known at admission); and (8) patients that are pregnant (if known at admission).

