#### Safety: complication rate during hospitalization

A complication rate during hospitalization will be calculated to determine the safety of C1-INH. This rate includes serious adverse events possibly related to study medication. This includes venous thromboembolic events (deep venous thrombosis and pulmonary embolism), myocardial infarction, ischemic stroke, meningitis, pneumonia, and sepsis. Patients will be assessed daily by a blinded physician/nurse for these complications. Vital signs will be monitored closely and potential adverse reactions to the experimental treatment will be picked up immediately at the ICU.

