### Statistical analysis

The trial profile will be summarized using a Consolidated Standards of Reporting Trials (CONSORT) flow diagram, including the reasons for non-eligibility and non-enrollment [52]. The data will be analyzed on an intention-to-treat basis with all randomized patients included in the analysis. Baseline variables will be summarized using descriptive statistics. In line with the IMPACT recommendations, the investigators plan to analyze the primary outcome TIL by using a linear model with covariate adjustment for age, GCS, and pupillary reactivity to adjust for baseline imbalances and to optimize statistical efficiency [53]. TIL will be analyzed as the TILmax for each patient, and the median for each group will be calculated. The treatment effect estimated will be based on the adjusted mean differences including 95% confidence intervals. To maintain the 5% familywise error rate, while still comparing the multiple clinically relevant endpoints, we will use a serial gatekeeping approach for statistical testing [54]. Analysis of GOSE at 6 months, as an ordinal outcome, will be done only if a significant difference in TIL is found. The co-primary endpoint GOSE will not primarily be used to declare the study success. For the analysis of GOSE at 6 months, covariate adjustment for the strongest predictors of outcome in TBI will be performed as mentioned above. The effect estimate will be an adjusted proportional odds ratio with 95% confidence interval for the shift in the direction of a better outcome on the GOSE. The ordinal regression model assumes that the odds ratio for each potential cut of the GOSE is constant no matter which cutoff point is taken (proportional odds assumption). Although the common odds ratio is formally only valid if the proportional odds assumption is met, the common odds ratio can be interpreted as a summary measure of treatment effect, even if the odds ratios differ by cutoff [55, 56]. In this study, the resulting single, common odds ratio can be interpreted as the average shift over the GOSE scale at 6 months caused by C1-INH compared to placebo [56].

Secondary analyses will be compared between the treatment groups using unadjusted and adjusted (ordinal) logistic and linear regression. Time-to-event analyses will be undertaken using Kaplan-Meier curves, as well as Cox proportional hazards regression models.

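### The primary safety endpoint has an analysis set made of events rather than patients, leaves open whether events are filtered by judged relatedness, and has no stated between-arm estimate

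*Protocol article*

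**What the plan says.** The protocol article's Objectives section names as a primary endpoint "2) safety: complication rate during hospitalization", alongside TIL and GOSE.

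The endpoint section (Safety: complication rate during hospitalization) says a rate will be calculated and continues: "This rate includes serious adverse events possibly related to study medication". It then gives a list: "This includes venous thromboembolic events (deep venous thrombosis and pulmonary embolism), myocardial infarction, ischemic stroke, meningitis, pneumonia, and sepsis". On ascertainment it says: "Patients will be assessed daily by a blinded physician/nurse for these complications".

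The section Safety and adverse event analysis says the safety analyses "will be based on the safety set, consisting of the pre-defined SAEs, and will comprise standard descriptive methods". It adds that changes from baseline will be summarized with shift tables. Relationship to the drug is one of the details recorded for each event.

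The Statistical analysis section says: "The data will be analyzed on an intention-to-treat basis with all randomized patients included in the analysis". On multiplicity it says "we will use a serial gatekeeping approach for statistical testing", and the sequence it describes runs from TIL to GOSE. TIL gets an adjusted mean difference and GOSE an adjusted common odds ratio, each with a 95% confidence interval. No effect measure is given there for the complication rate.

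**The concern.** Three features of the stated text leave this primary endpoint badly fixed.

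- **Analysis set.** A safety set is normally a set of patients. One composed of events has no denominator, and it is a different object from the all-randomized population named for the trial's data in general. The reader cannot tell whether the rate is per randomized patient, per dosed patient, or a count of events.
- **Relatedness.** The phrase about possible relation to study medication allows two readings. Either the listed event types were considered possibly related in advance, and all of them count, or each event is judged and only those thought possibly related count. The two give different numerators. With randomization and placebo, the comparison of arms addresses causality, so a case-by-case judgement adds nothing to the endpoint and removes events from it.
- **Method.** Change from baseline and shift tables suit laboratory values or vital signs. For a rate, the natural summary is a proportion by arm and their difference, with an interval.

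Safety is half of the main objective, and the results are meant to inform a phase III trial. Without an interval, a reader cannot see how large an excess of infection or thrombosis the trial leaves open.

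**Working it through.** **1. What the sample size was built for.** The only sizing figure is 106 patients, 53 per arm, and it rests on TIL: difference 2.2, SD 3.2, two-sided 0.05, power 90%, about 10% loss (Sample size section).

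- Normal approximation: n = 2 × (1.96 + 1.2816)² × 3.2² / 2.2² = 44.5, so 45 per arm.
- The two-sample t-test needs 45.4, so 46 per arm. 46 / 0.9 = 51.1, so 52 per arm, or 104 in total.

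This is within two patients of 106, so the figure reproduces. It says nothing about the precision of the complication rate, for which the article gives no expected value.

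**2. Precision of a by-arm complication rate.** Inputs: 53 per arm (Sample size section), and a rate p assumed equal in both arms. The values of p are assumptions. Half-width of the 95% CI for the risk difference = 1.96 × √(2p(1 − p)/53).

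| Assumed p | 2p(1 − p)/53 | Half-width |
|---|---|---|
| 10% | 0.00340 | 11.4 points |
| 20% | 0.00604 | 15.2 points |
| 30% | 0.00792 | 17.4 points |
| 40% | 0.00906 | 18.7 points |
| 50% | 0.00943 | 19.0 points |

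**3. Direction of a relatedness filter.** Suppose each affected patient has one event and blinded assessors judge the same share s of events possibly related in both arms. Rates p₀ and p₁ then become s·p₀ and s·p₁, and the difference becomes s·(p₁ − p₀). For illustration only, take 30% against 40% with s = 0.5. This gives 15% against 20%: the difference falls from 10 to 5 points, while the ratio stays at 1.33 but rests on half the events. If patients have several events, the proportion with at least one related event falls less. The documents give neither rates nor s, so only the direction is claimed.

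**4. The passages side by side.** The endpoint section promises a rate. The general analysis rule supplies all randomized patients as a denominator. The safety analysis section names another set and describes it by its events. The text does not say which governs.

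**The case against.** The strongest reply is that the plan still yields a usable comparison. A rate is promised, the intention-to-treat statement supplies a denominator for each arm, and blinded staff look for the listed events every day. That stands. A reader might infer that no valid between-arm complication rate can be obtained, but the documents do not support this: counts by randomized arm under blinded assessment are valid, if imprecise.

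The relatedness phrase is followed at once by a fixed list. The analysis section calls these events pre-defined and records relationship to the drug as one detail per event. On that evidence the list may simply name types considered possibly related in advance. This reading is plausible and cannot be excluded; the fault is that the text permits the other one too. Nor do the documents show what share of events would be attributed to the injury. Because assessors are blinded, a filter would mainly dilute the difference and would not be expected to favor an arm.

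Descriptive safety reporting is usual in phase II, a formal test is not required, and the detail of a safety set may be in a statistical analysis plan. This also stands, so the absence of a test is not criticized. The wording that is present is still a misdescription of the set, and shift tables are still the wrong tool for a rate.

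A reader might infer that the plan would declare safety by default. That goes too far: the DSMB sees unblinded adverse events and mortality at scheduled points, and all-cause mortality is a secondary endpoint.

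Finally, the exclusion criteria refer to a "history of thrombosis (deep vein thrombosis, cerebral venous sinus thrombosis, or pulmonary embolism", while the complication list names only deep venous thrombosis and pulmonary embolism. A reader might take this for a contradiction. It is not: one list screens medical history and the other names in-hospital outcomes, and they need not match.

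**Conclusion.** This is a real defect of definition, moderate in weight, that should be corrected. The safety set is described by events, it does not fit the all-randomized analysis, and the named summaries do not suit an event rate. The relatedness wording leaves two different numerators open, one of which would shrink an absolute excess towards no difference.

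The trial can still produce a by-arm rate. Its 95% confidence interval for the risk difference is about ±11 to ±19 points, assuming rates of 10% to 50%, equal in both arms, and all 53 patients per arm in the denominator. A smaller dosed set would widen it. The sample size sets that limit, and correcting the definition does not remove it; reporting the interval makes it visible. No size is attached to the dilution, because the documents give no attribution share.

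**What to change.** - Define the safety set as patients, for example all randomized patients who received study drug, and state how it relates to the all-randomized population under Statistical analysis.
- Define the endpoint as the proportion of patients with at least one listed complication during hospitalization, regardless of judged relatedness.
- Report it by arm with the risk difference and 95% CI. State that this is estimation and lies outside the TIL-to-GOSE testing sequence.
- Keep judged relatedness as a separate listing, and confine change-from-baseline and shift tables to measurements that have a baseline.

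The cost is wording in the protocol and the statistical analysis plan, plus one extra estimate. The listed complications are already assessed daily and relatedness is already recorded, so no new data or patients are needed.

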### Patient and public involvement

Patients and their caregivers have been involved in the research design, including selection of outcome measures and feasibility of the trial interventions and follow-up. The patient panel and their caregivers will be informed about the developments of the study and will be invited to participate in research meetings and discussions.

### Ethics

The study protocol was designed in accordance with the ethical principles in the Declaration of Helsinki and the regional regulations, and the principles of Good Clinical Practice. Participants will be assessed for eligibility by the neurosurgical resident or research physician when an ICP monitor is placed within 12 h from trauma. Within this time frame, informed consent must also be obtained. Ideally, the treating physician will obtain informed consent from the patient. As the enrolled subjects will lack capacity to consent due to their level of consciousness at presentation, informed consent can be obtained within 12 h after trauma by a legally authorized representative of the patient. As TBI mostly occurs outside the domestic situation, family members are rarely available during the first hours after trauma [57]. Therefore, the treating physician will take responsibility for including the patient using “deferred proxy consent” if the following condition are met and documented: (1) the patients is in a potentially life-threatening situation and (2) the patient meets the eligibility criteria for trial entry. As there is a potential benefit with the administration of C1-INH and an urgent therapeutic timeframe of 12 h, deferred consent is justified in these patients [58–60]. Following enrollment via deferred consent, informed consent should still be obtained by a legal representative within 7 days after admission. Furthermore, the patient must agree to further participate in the study when mental capacity is regained. When consent for study continuation is provided, already collected data can be used. When study continuation is refused, already collected data can still be used when patients and/or proxies do not use their right to refuse this. Patients or proxies should always be informed about their right to refuse the use of obtained data. A team of dedicated research nurses and physicians are trained to perform the specific informed consent and randomization procedures. Moreover, a 24/7 study consultation telephone number can be reached to help with problems or questions during the study.

### Reporting and dissemination

Reporting of our study will follow the CONSORT guidelines [52]. The results of this study will be presented at national and international scientific conferences and will be published in peer-reviewed journals without any publication restrictions. All authors who fulfil the authorship criteria will be included in future publications. There is no intended use of professional medical writers. Furthermore, the results of the current trial will inform a phase III clinical trial with a large and pragmatic enrollment rate powered solely on efficacy regarding clinical outcome improvement.

### Trial status

The trial will be conducted according to the protocol, version 7.0 (February 2021). Recruitment of subjects is intended to start February 2021 and target recruitment should be achieved by February 2023, making final outcomes available by the end of 2023.

## Data Availability

Final study datasets will be stored locally and securely at Leiden University Medical Center for long-term storage and access. These datasets will be available for researchers actively contributing to statistical analyses and publications. Data will be available upon request. Requests can be made with the corresponding author.

## Abbreviations

C1-INH: Complement 1-inhibitor
DSMB: Data Safety Monitoring Board
EQ-5D-5L: 5 Level EuroQoL 5-Dimensional Questionnaire
GCS: Glasgow Coma Scale
GOSE: Glasgow Outcome Scale Extended
ICP: Intracranial pressure
iPCQ: IMTA Productivity Cost Questionnaire
iMCQ: IMTA Medical Consumption Questionnaire
MAC: Membrane attack complex
PI: Principal investigator
SAE: Serious adverse event
SF-36: Short-Form 36
TBI: Traumatic brain injury
TIL: Therapy Intensity Level
QoLiBri: Quality of Life after Brain Injury Scale
